A routine CAD screening induces high healthcare expenses as it leads to invasive investigations, endovascular and surgical revascularizations as well as intensification of pharmacological therapies. To the best of our knowledge, the cost-effectiveness of routine CAD screening has not been evaluated prospectively in population with T2DM and a very high cardiovascular risk. Only two economic studies, based on Markov models, have addressed this question by comparing different strategies in Japanese and American populations: no screening, screening (with stress echocardiography, myocardial scintigraphy coupled with stress test, or stress electrocardiogram) [21, 22]. Their results were very limited by model’s hypothesis; uncertainty surrounding epidemiological and utilities data used; and costs of care, which may differ greatly across countries. In this context of discrepancy between lack of evidence and current guidelines and clinical practice, we aim to estimate the effectiveness and cost-effectiveness of systematic CAD screening in patients with T2DM and a very high cardiovascular risk.

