#### Exclusion criteria

One of the following:The presence of CAD (defined as a history of acute coronary syndrome, coronary revascularization, angina pectoris, or unstable angina).Any visit to an emergency department for chest pain resulting for admission to a cardiac intensive care unit.

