### Study groups and methods of CAD screening

#### Screening group

Individuals who had at least one screening exam (stress electrocardiogram test, stress echocardiography, myocardial scintigraphy coupled with stress test or pharmacological stimulation using adenosine, or coronary CT scan) (Table 2) during the selection period (2008–2015).

**Table 2 Tab2:** Codes used to identify tests to screen coronary artery disease

Tests	Procedure codes
Stress test	DKRP004, EQRP002, EQRM001
Myocardial scintigraphy coupled with stress test or pharmacological stimulation using adenosine	DAQL001, DAQL010, DAQL011, DAQL009
Stress echocardiography	DAQM003, DZQM002, DBQM001
Coronary CT scan	ECQH010
Procedure codes: Codes of the French classification of medical procedure (CCAM)	

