#### No-screening group

Participants who never experienced a screening exam as described above during the selection period (2008–2015), except resting electrocardiogram.

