### Statistical analysis plan

The data will be analysed by the biostatistician of the “Clinical Epidemiology Unit” of the University Hospital of Bordeaux (USMR). Analyses will be performed using SAS® software, version 9.4 or later (SAS Institute, Cary, NC, USA, http://www.sas.com) and all tests will be performed at the first-order error risk α = 5%. The flow-chart (CONSORT), as well as the characteristics of patients at inclusion (eligibility criteria, epidemiological, clinical, biological characteristics and treatment use) will be presented. Confounding factors will be taken into account through a hdPS score that will involve around 500 variables, according to the Bross formula [26]. A principal component analysis will then allow us to reduce the dimensionality to 30 components, and the goodness of fit of this hdPS score will be estimated by a graphical comparison of the score distribution and by standardized mean differences between the two study groups [27]. Comparisons between the two groups will be carried out with and without adjustment for the hdPS score, and the hypotheses of the different regression models chosen, will be systematically verified.

Regarding the analysis of the primary endpoint, a gross estimate of the incremental cost per life-year gained at 5 years will be conducted. The confidence interval (CI) of this incremental cost-effectiveness ratio will be estimated by boostrap (5000 iterations). The analysis will be performed as Intent to Treat. To investigate a possible relationship between the frequency of screening and survival, we will define four different subgroups: screening conducted at least once a year, less than once a year (and at least once every two years), less than once every two years (and at least once every three years), and only once during the follow-up period.

A cost-consequence analysis will be performed linking results of all direct costs (observed during the following period) and results on major cardiovascular events. A budget impact analysis will be conducted to determine the public expenses of the spread of a systematic screening for silent ischemic CAD.

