### Strengths and limitations

The key strength of our study is the collection of a comprehensive range of clinical features, cardiovascular procedures, history of pharmacological therapies or surgery, major events and survival status in the whole French population of patients with T2DM and a very high cardiovascular risk during an overall period of 12 years. SCADIAB findings will have a broader generalizability for all T2DM patients at a very high cardiovascular risk. Our study will provide a line of complementary evidence (further to RCTs’ findings) in terms of routine CAD screening in a contemporary cohort of patients with T2DM in real-world settings. SCADIAB will be more economical and time efficient than RCT, but a number of intrinsic limitations need to be acknowledged. The retrospective and non-randomized design of our study is subject to bias (selection, information, detection) and confounding factors. To limit selection bias, our study population will be rigorously defined using pre-specified inclusion criteria (T2DM for at least 7 years, with at least 2 cardiovascular risk factors and one or more organ damage) extracted from reliable and valid SNDS database. The 7-year selection period leading to assignment of each individual to one of the two study arms (CAD screening or absence of CAD screening) will limit information bias. We will use validated algorithms to identify inclusion criteria and endpoints [29–31]. Also, the cardiovascular investigation required for study arms assignment (stress test, scintigraphy, stress echocardiography…) will be recorded exhaustively in the SNDS database. We believe that the detection bias will be limited in our study as we have access to the SNDS database covering the whole French population including death registry. Finally, we will use the hdPS method to control measurable confounding factors as well as unknown or unmeasurable ones [32–34].

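### The screening arm is defined by any listed coronary test regardless of indication, so the contrast is any non-invasive test versus none rather than screening for silent CAD, and hdPS is credited with controlling confounders it cannot see

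*Protocol article*

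**What the plan says.** The Background of the protocol article states the target: "we aim to estimate the effectiveness and cost-effectiveness of systematic CAD screening in patients with T2DM and a very high cardiovascular risk". It introduces the problem as one of silent disease in asymptomatic people. The Statistical analysis plan section says the budget impact analysis will determine "the public expenses of the spread of a systematic screening for silent ischemic CAD".

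The exposure is defined differently. The Screening group consists of "Individuals who had at least one screening exam" during the selection period, the exams being stress ECG, stress echocardiography, myocardial scintigraphy and coronary CT. Table 2, titled "Codes used to identify tests to screen coronary artery disease", lists procedure codes and nothing else. The comparator is "Participants who never experienced a screening exam as described above during the selection period (2008–2015), except resting electrocardiogram". Neither definition refers to why a test was done.

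There are two exclusion criteria. The first is "The presence of CAD (defined as a history of acute coronary syndrome, coronary revascularization, angina pectoris, or unstable angina"). The second is "Any visit to an emergency department for chest pain resulting for admission to a cardiac intensive care unit".

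On confounding, Strengths and limitations says that "we will use the hdPS method to control measurable confounding factors as well as unknown or unmeasurable ones". The Methods part of the Abstract makes the same kind of claim, for known and unknown confounders.

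**The concern.** A procedure code records that a test was done, not the reason for it. A stress test ordered for exertional dyspnoea and one ordered for an asymptomatic patient carry the same code and enter the same arm. If the first kind is common, the study estimates the effect and cost of having a coronary test for any reason. That is a different question from whether routine screening of asymptomatic patients is worth paying for. The mismatch carries into the primary endpoint (cost per life year saved), the screening-frequency subgroups, the budget impact and the reported frequency of routine screening.

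The statement about hdPS makes this worse, because it tells readers that unmeasured confounding has been handled. The indication for a test is only partly visible in claims, and a propensity score cannot balance the part that is not recorded or proxied. Even complete balance would leave the exposure label wrong.

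**Working it through.** **The plan's own figure.** Sample size estimation gives 2.4 million people with T2DM free of CAD, 38% with at least two risk factors and more than 10% with vascular disease. The product is 2,400,000 × 0.38 × 0.10 = 91,200, which agrees with the stated minimum of 90,000. This is a feasibility count and the present point does not change it. A large sample narrows the interval around the estimate but does not remove bias.

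**Who passes the exclusions.**
- History of acute coronary syndrome, coronary revascularization, angina pectoris or unstable angina: excluded.
- Emergency visit for chest pain with admission to cardiac intensive care: excluded.
- Emergency visit for chest pain without that admission, and not coded as angina or other CAD: not excluded.
- Outpatient chest pain or dyspnoea never coded as CAD: not excluded.
- Test before vascular surgery or transplantation: not mentioned anywhere. That such tests enter the screened arm is an inference from the code-only definition, in a cohort selected partly for peripheral artery disease, carotid stenosis and CKD.

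A listed test in any of the last three situations puts the patient in the screened arm.

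**Illustration of size.** Let q and p be the shares of symptomatic patients in the screened and control arms, and r their risk ratio against asymptomatic patients that remains after adjustment. If screening has no effect, the apparent ratio is

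[1 + q(r − 1)] / [1 + p(r − 1)].

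The documents give none of q, p or r; all are assumptions.

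With p = 0:
- q = 10%, r = 1.5: 1 + 0.10 × 0.5 = 1.05
- q = 30%, r = 1.5: 1 + 0.30 × 0.5 = 1.15
- q = 30%, r = 2.0: 1 + 0.30 × 1.0 = 1.30

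With symptoms in controls too, taking p = 10%:
- q = 30%, r = 2.0: 1.30 / 1.10 = 1.18

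With r below 1, taking the reciprocal of 1.5 (0.667) and p = 0:
- q = 30%: 1 + 0.30 × (0.667 − 1) = 0.90

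**Against a benchmark.** The Discussion cites a 20% relative risk reduction, a ratio of 0.80. With p = 0 that benefit is fully masked when 0.80 × [1 + q(r − 1)] = 1, that is q(r − 1) = 0.25. Examples are q = 25% with r = 2.0, or q = 50% with r = 1.5.

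**The case against.** The strongest reply is that the plan already does much of what is needed. Four parts of it deserve weight.

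- **Exclusions.** A reader might infer that emergency chest pain leading to intensive care is the only symptom-related exclusion. It is not: recorded angina, unstable angina, acute coronary syndrome and revascularization are excluded too, in both arms. This stands, and it narrows the gap to symptoms never coded as CAD.
- **Direction.** A reader might infer that the screened arm must look sicker and costlier. The documents do not support that. The selection period is used to establish eligibility and a history of CAD excludes, so a symptomatic patient whose test led to coded angina or revascularization in that period would, on a plain reading, be removed. Those left may be disproportionately test-negative, and r could be below 1.
- **Adjustment.** The score draws on around 500 variables measured in the selection period, and could pick up heart failure codes or anti-anginal deliveries. This stands as a reason to read r as a residual and to expect a smaller bias. It does not reach symptoms that leave no claim, and it does not turn a test done for symptoms into screening.
- **Acknowledged limitation.** Strengths and limitations concedes selection, information and detection bias and confounding in general. It does not mention test indication. Nor does it say that hdPS is meant to deal with indication in particular, and a reader should not take it that way. The error is the general claim about unknown or unmeasurable confounders.

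**Conclusion.** The point holds in this limited form. As written, the plan compares any non-invasive coronary test with none, and it presents the result as evidence on systematic screening for silent CAD. The exclusions remove coded CAD and the most severe emergency chest pain, but not symptoms outside those categories. The statements that hdPS takes care of unknown or unmeasurable confounders are wrong as worded.

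Neither the size nor the direction of the bias can be read from the documents. Under the assumptions above, a null effect would appear as 1.05 to 1.30. It moves closer to 1 if controls are also symptomatic, and falls below 1 if r < 1 and q > p. A comparison of this bias with the width of the study's confidence interval is tempting, but the documents give no event rate for this cohort and no split between the arms, so none is made here. The mismatch between exposure and question does not depend on any of these values.

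**What to change.** - **Exposure.** Count an exam as screening only if no claims marker of symptoms falls in a fixed window before it, for example 90 days. Markers would be a code for chest pain, dyspnoea, syncope, heart failure or arrhythmia, or a first anti-anginal delivery.
- **Controls.** Apply a matching symptom-free rule. Controls have no test date, so the rule must name a reference date. Use only information dated before the index date of 1 January 2015 in both arms.
- **Pre-operative tests.** Identify them only through surgery dated before the index date. Do not exclude on later events: carotid and lower-limb revascularization and kidney transplantation are endpoint components, and removing them from one arm would create a new bias.
- **Unclassified patients.** Those whose only tests fail the rule would fit neither arm as the No-screening group is now worded. Say so and report their number.
- **Sensitivity analysis.** Report the any-test definition alongside. At minimum, if the rule is not adopted, relabel the exposure as any non-invasive CAD test and limit the conclusions and budget impact accordingly.
- **hdPS wording.** In the Abstract and in Strengths and limitations, claim control of measured and proxied confounders only. A negative-control outcome or an E-value is an optional addition.

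The cost is protocol wording and extra code lists. Study progress says that database access was still being arranged, so no analysis has to be redone. The drawbacks are fewer screened patients, and outpatient symptoms that leave no claim will still be missed.

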### Recruitment of participants and follow‑up

The data will be extracted from January 1, 2008 to December 31, 2019. A selection period will be defined by the 7 years (January 1, 2008 to December 31, 2014) preceding the index date. It will enable us to identify eligible patients and measure all the variables needed for the calculation of the high dimension propensity score (hdPS). Each participant will be assigned to one of the two study groups on the index date (January 1, 2015), and then followed up to December 31, 2019 (Fig. 1).

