**Methods:**

SCADIAB is a comparative nationwide cohort study using data from the French National Health Data System. The main inclusion criteria are: age ≥ 40 years, DT2 diagnosed for ≥ 7 years, with ≥ 2 additional cardiovascular risk factors plus a history of microvascular or macrovascular disease, except CAD. We estimated ≥ 90,000 eligible participants for our study. Data will be extracted from 01/01/2008 to 31/12/2019. Eligible participants will be identified during a first 7-year selection period (2008–2015). Each participant will be assigned either in experimental (CAD screening procedure during the selection period) or control group (no CAD screening) on 01/01/2015, and followed for 5 years. The primary endpoint is the incremental cost per life year saved over 5 years in CAD screening group *versus* no CAD screening. The main secondary endpoints are: total 5-year direct costs of each strategy; incidence of major cardiovascular (acute coronary syndrome, hospitalization for heart failure, coronary revascularization or all-cause death), cerebrovascular (hospitalization for transient ischemic attack, stroke, or carotid revascularization) and lower-limb events (peripheral artery disease, ischemic diabetic foot, lower-limb revascularization or amputation); and the budget impact for the French Insurance system to promote the cost-effective strategy. Analyses will be adjusted for a high-dimension propensity score taking into account known and unknown confounders. SCADIAB has been funded by the French Ministry of Health and the protocol has been approved by the French ethic authorities. Data management and analyses will start in the second half of 2021.

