### Study population

#### Inclusion criteria

Eligible participants must meet all of the following criteria:Age = 40 years or older,Affiliation to the general health insurance scheme in France,Diagnosis of T2DM,Duration of T2DM ≥ 7 years,Two or more additional cardiovascular risk factors (obesity, hypertension, hypercholesterolemia, or tobacco smoking using the chronic obstructive pulmonary disease (COPD) as a proxy),At least one microvascular or macrovascular disease: carotid stenosis, transient ischemic attack (TIA), stroke, lower-limb peripheral artery disease (PAD), CKD, severe diabetic retinopathy with requirement of laser photocoagulation, or peripheral or autonomic diabetic neuropathy.

Diagnosis will be determined based on the list of 100% health insurance coverage for chronic diseases in France (including T2DM, hypertension, TIA, stroke, PAD, CKD, COPD), the history of diseases of interest or surgery (coronary, carotid or lower-limb revascularization, bariatric surgery, kidney transplantation) according to the International Classification of Diseases Code Tenth Revision (ICD-10) (Additional file 1: Table S1), or at least 3 deliveries of one or more corresponding drugs as appropriate (antidiabetic, anti-obesity, antihypertensive or lipid-lowering drugs) over one year.

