### Cost-effectiveness of routine CAD screening in patients with diabetes

Systematic CAD screening strategy leads to more invasive examination, especially coronary angiography, which is associated with increased risk of complications [11, 12]. Routine CAD screening encourages also revascularizations and intensification of pharmacological treatments, despite uncertainties in terms of related benefits. In the FACTOR-64 study, CAD screening was not associated with a significant reduction in major cardiovascular events despite intensive pharmacological control of cardiovascular risk factors (and some coronary revascularizations) in patients with a positive screening test, while individuals assigned to control group and those with a negative screening test had only conventional cardiovascular treatment goals [13]. Furthermore, BARDOT (Basel Asymptomatic high-Risk Diabetics' Outcome Trial) study showed that combined medical therapy and invasive strategy (coronary angiography followed or not by revascularization) for silent CAD, compared with medical treatment alone, was associated with reduced scintigraphic CAD progression, but no significant difference was observed in terms of hard clinical events in high risk T2DM patients [28]. Therefore, to avoid unjustified health expenses and misuse of collective resources associated with routine CAD screening, we conduct the SCADIAB study to assess the cost-effectiveness of this strategy in people with T2DM and a very high cardiovascular risk.

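### Eligibility and screening exams are read from the same 2008-2014 window with no order between them, so exams done before a patient was at very high risk count as screening, and a drug started after an exam can create eligibility in the screened arm only

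*Protocol article*

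**What the plan says.** In the protocol article, Recruitment of participants and follow-up sets the window: "A selection period will be defined by the 7 years (January 1, 2008 to December 31, 2014) preceding the index date". The same section says of this period "It will enable us to identify eligible patients", and also has it supply the propensity-score variables. The Screening group section takes exposure from the selection period too: "Individuals who had at least one screening exam" of the Table 2 types. The No-screening group section requires that there was none. Groups are assigned on 1 January 2015 by looking back over the window.

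Inclusion criteria asks for at least 7 years of type 2 diabetes, two or more further risk factors and at least one micro- or macrovascular disease. No criterion is dated relative to the exam, and the date at which the 7 years is read is not given. Diagnoses can be established by coverage status, by coded history or by "at least 3 deliveries of one or more corresponding drugs as appropriate (antidiabetic, anti-obesity, antihypertensive or lipid-lowering drugs) over one year".

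The discussion of cost-effectiveness states that "Routine CAD screening encourages also revascularizations and intensification of pharmacological treatments".

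(The abstract and the two group definitions label the window 2008-2015. The dated version, ending 31 December 2014, is used here.)

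**The concern.** The Background states the aim as the effectiveness and cost-effectiveness of screening in patients at very high cardiovascular risk. With no order between qualifying and being examined, two things follow.

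- **Exposure outside the target population.** A patient examined before reaching very high risk, and not again, is labelled as screened although no screening of a very-high-risk patient took place. This blurs the contrast. The article does not allow a direction to be assigned.
- **Exposure that creates eligibility.** If an exam leads to a new lipid-lowering or antihypertensive drug, three deliveries in a year can supply the second risk factor and bring the patient into the cohort. The same patient, unexamined and untreated, stays out of the control arm. This is selection on a consequence of exposure. If such patients are at lower risk than the rest of the cohort, it makes screening look better than it is.

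The group definition underlies the primary cost per life year saved and every Cox comparison, so both effects would carry through to all results.

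**Working it through.** **The plan's own figure.** Sample size estimation gives 2.4 million people with type 2 diabetes and no history of CAD, 38% with two or more risk factors, and more than 10% with vascular disease. The product is 2,400,000 x 0.38 x 0.10 = 91,200, which agrees with the stated minimum of 90,000. It contains no dates of qualification or of exams, so the number of misplaced exams cannot be derived from it.

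**Two patients followed through the stated rules.**

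1. Diabetes diagnosed in 2007 and hypertension present; stress test in 2008; lipid-lowering drug from 2009; peripheral artery disease in 2013. If duration is read at the index date, which the article leaves open, all criteria are met by 1 January 2015. The patient is in the screening group on the strength of an exam done with about one year of diabetes, one risk factor and no organ damage.
2. Ten years of diabetes, CKD and hypertension as the only risk factor; exam in 2011; lipid-lowering drug then started and delivered three times within a year. The patient now has two risk factors and enters the screening group. The same patient with no exam and no drug has one risk factor and is not in the study.

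**Size of the timing problem, under assumptions not in the document.** Let a share f of eligible patients complete the criteria at a time spread uniformly over the window of W = 7 years, the rest having qualified before 2008. Let exams occur independently of qualification at rate r per year (Poisson). Patients who are never examined are controls and do not affect the share within the screening group.

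For a patient qualifying at time t, the chance of at least one exam before t and none after is (1 - exp(-rt)) x exp(-r(W - t)). Averaging over t and dividing by the chance of any exam, 1 - exp(-rW), gives

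share with all exams before qualification = f x [1/(rW) - 1/(exp(rW) - 1)].

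The physician survey in the Background reports frequencies of once a year (42%), once in two years (20%) and once in three years (33%), so r = 1, 1/2 and 1/3 are natural values.

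| Exams | Bracket | f = 0.25 | f = 0.5 | f = 1 |
|---|---|---|---|---|
| r = 1 | 0.142 | 3.5% | 7.1% | 14.2% |
| r = 1/2 | 0.255 | 6.4% | 12.7% | 25.5% |
| r = 1/3 | 0.321 | 8.0% | 16.1% | 32.1% |
| r = 1/7 | 0.418 | 10.5% | 20.9% | 41.8% |
| one exam, uniform | 0.500 | 12.5% | 25% | 50% |

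**Size of induced eligibility, under assumptions not in the document.** Let the near-eligible pool be k times the eligible pool, let screening cause a new qualifying drug in a fraction q of it, and let mortality be 5% per year in eligible and 3% in near-eligible patients, with no true effect of screening. The induced share of the screened arm is kq/(1 + kq).

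- k = 0.3, q = 0.2: 0.06/1.06 = 5.7%; mortality 5 - 2 x 0.057 = 4.89; ratio to controls 4.89/5 = 0.98.
- k = 1, q = 0.3: 0.30/1.30 = 23.1%; mortality 5 - 2 x 0.231 = 4.54; ratio 4.54/5 = 0.91.

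All four inputs are assumed. The calculation shows the direction when induced patients are at lower risk; it does not estimate the size.

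**The case against.** The strongest reply is that everyone is at very high risk on 1 January 2015 and is followed from then, so the comparison is of screening histories among patients who are eligible at index. That is a coherent estimand for the timing issue, and choosing an eligibility date is partly a choice of estimand. It does not answer the second issue: being eligible at index does not help when the exam is what made the patient eligible.

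Several limits on size stand:

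- A drug can complete only the risk-factor criterion. Organ damage and diabetes duration are still needed.
- Intensifying a drug already taken changes nothing. Only a newly started qualifying class does.
- In the trial that the article uses as its example, intensive control went to patients with a positive test. Those later coded with angina or revascularised leave through the CAD exclusion.
- Repeat exams reduce the timing problem, because one exam after qualification is enough to place the patient correctly.

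A reader might go further and infer that half of the screening group is misplaced. If duration D is read at index and a single exam is uniform over the 7 years, the chance that it came before the 7-year mark is (14 - D)/7, which is 100% at D = 7 and averages 50% over durations of 7 to 14 years. That average leaves out everyone with 14 or more years, who contribute nothing, and it allows only one exam. The article gives no distribution of duration to support it.

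A reader might also infer that the propensity score cannot help at all. That is too strong. With around 500 candidate variables, a shared drug class does not make a lower-risk patient identical to a higher-risk control, and partial correction is possible. It cannot be relied on, because its variables come from the same window and may follow the exam.

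Fig. 1 and the full protocol are not at hand, but the text itself fixes the shared window.

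**Conclusion.** The concern holds as a fault in a stated design rule. Followed as written, the plan counts exams done before a patient was at very high risk, and lets a drug started after an exam create eligibility in the screened arm only.

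The size is not derivable from the document. With exams at 1/3 to 1 per year, about 4-8% of the screening group would have all exams before qualification if a quarter of patients qualify inside the window, and about 7-16% if half do. Single exams raise this to 12.5% and 25%. These figures assume uniform qualification times and exams independent of qualification.

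The induced-eligibility bias favours screening only if the added patients are at lower risk. It may be small: the milder scenario gives a ratio of 0.98, and 0.91 needs a near-eligible pool as large as the eligible one together with a 30% excess of new drug starts. The documents do not support quoting 0.91 as the expected bias or concluding that the primary result is invalid. They do support settling the order before the cohort is built.

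**What to change.** Amend Recruitment of participants and follow-up, Screening group and No-screening group as follows.

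1. Define for every patient, by one rule for both arms, an eligibility date on which all inclusion criteria are first met. State how diabetes duration is dated when there is no coverage start date, for example when diabetes is identified from drug deliveries. Alternatively, require all criteria to be met before a common date that opens the exam window.
2. Define the screening group by at least one Table 2 exam on or after that date, and the no-screening group by none on or after it.
3. Treat an exam before that date in the same way in both arms, as a baseline covariate. Add a sensitivity analysis that leaves out everyone with a pre-eligibility exam, whatever their arm.

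Do not simply exclude patients whose qualifying drug or diagnosis code follows their first exam. Controls have no exam, so such a rule would act on the screened arm alone. It would remove patients with newly recorded organ damage there while keeping them as controls, which could create a new bias in favour of screening. It would also conflict with step 2 for patients examined both before and after qualifying.

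The cost is protocol wording, some reprogramming of cohort selection on dated claims that are already to be extracted, and a smaller screening group.
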